#### 2.6.5 Elements to directly reach members of the target populations or their relatives

After the first round of process evaluation, virtual and non-virtual learning formats for risk groups and family members were added to address the target population more directly. Short video formats were developed for the purpose of being displayed in the waiting areas of hospitals or doctor’s offices and implemented in several waiting areas at Charité University Hospital. In cooperation with a large health insurer, we targeted family caregivers with educational material for family caregivers and short information formats for publication on a dedicated online platform and to be handed out to laypeople in seminars (open to people with any health insurance).

None of the mentioned intervention elements were expected to result in any adverse events or harm for recipients or participants. All members of the consortium participated in a planned process evaluation (see 2.9 Process evaluation–Evaluation of the implementation), including interim analyses of available data and the option to adapt the implementation strategy.

### 2.7 Implementation of the campaign

Start date for the implementation of the SepWiss campaign was August 11^th^, 2021. Not all elements of the campaign could be finalized and implemented with the launch of the campaign. The ongoing COVID-19 pandemic necessitated an initial focus on developing virtual educational formats in the first half of the campaign, and in-person formats only became possible when contact restrictions due to the pandemic subsided. In addition, some elements of the campaign could not be implemented before additional stakeholders like regional media outlets and professional associations had been contacted and involved. Thus, the different elements of the campaign were implemented consecutively, as depicted in Fig 1.

### 2.8 Evaluation of the intervention

#### 2.8.1 Assessment of the primary outcome

Primary outcome will be assessed by the partners at German public health institute Robert Koch–Institute (RKI) in Berlin.

We hypothesize that the intervention will have a positive impact on vaccination coverage of influenza, pneumococci, meningococci and haemophilus influenzae type b vaccination in the target population, and thus vaccination coverage will increase during the intervention period and will be higher in Berlin and Brandenburg (intervention region) compared to other federal states in Germany (control region). To test this hypothesis, vaccination coverages for aforementioned vaccinations are analyzed.

*2*.*8*.*1*.*1 Data source and population*. Data base are all outpatient claims data of all statutory health insured (SHI) individuals in Germany, covering approximately 87% of the general population. These data are routinely reported to RKI, and no sample size calculation was needed. The data set includes information about month and year of birth, sex, federal state of residence, type and date of vaccination and International Statistical Classification of Diseases (ICD-10) coded diagnoses. Detailed information on the data set is provided elsewhere [25].

Vaccination coverage can be calculated for influenza, pneumococci, meningococci and haemophilus influenzae type b vaccination in three different target populations based on the vaccination recommendations by the National Immunization Technical Advisory Group in Germany: (a) the elderly population aged 60 and above, (b) pediatric population aged three years and younger, and (c) population with vaccine-relevant pre-existing health conditions.

*2*.*8*.*1*.*2 Outcomes*. Outcome measures include vaccine coverage among the three target groups before / early in the intervention versus during its full implementation. Data from Berlin and Brandenburg will be analyzed versus the other federal states of Germany (control group). Data from the pre-intervention period (July 2016 until June 2021) will be compared to data from the post-intervention start period (July 2021 until December 2023).

*2*.*8*.*1*.*3 Statistical analyses*. We use a cohort approach to calculate vaccination coverage. This enables age-, sex- and region-specific analyses as well as an analysis of vaccine coverage in consideration of a health indication to vaccinate [25]. Vaccination coverage is calculated as the proportion of individuals among a cohort who received the vaccine within the influenza season (influenza or pneumococci) or as a single dose as an adult (meningococci and haemophilus influenzae type b). The results are reported as vaccination coverage per season and calendar year, respectively.

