### 2.3 Target population

The campaign was targeted to reach the adult population with known risk factors for developing sepsis from an underlying infection. Amongst others, these include:

older age (> 60 years)innate or acquired dysfunction of the immunosystem, such as immunodeficencies, immunopathies, HIV/AIDSlong-term treatment with systemic immunosuppressive medication (e.g. for rheumatic disorders or autoimmune diseases)underlying chronic conditions of the lung, heart or liveraspleniadiabetes mellitus

If one of these risk factors is present, vaccination against influenza and pneumococci is recommended according to the Standing Committee on Vaccination (STIKO); for asplenia, vaccination against haemophilus influenzae and meningococci is recommended [7].

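### One of the three primary-outcome groups, children aged three and younger, lies outside the adult population the campaign targeted, and the stated meningococcal and Hib coverage definition is 0% in it by construction.

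*Protocol article*

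**What the plan says.** Section 2.3 of the protocol article describes whom the campaign was for: "The campaign was targeted to reach the adult population with known risk factors for developing sepsis from an underlying infection". Its list of risk factors contains no paediatric group.

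Section 2.8.1 states the primary hypothesis as a positive effect on coverage of influenza, pneumococcal, meningococcal and "haemophilus influenzae type b vaccination in the target population, and thus vaccination coverage will increase during the intervention period". The data-source paragraph of the same section (2.8.1.1) then says: "Vaccination coverage can be calculated for influenza, pneumococci, meningococci and haemophilus influenzae type b vaccination in three different target populations". These are (a) people aged 60 and above, ("b) pediatric population aged three years and younger", and (c) people with pre-existing conditions relevant to vaccination, for whom no age limit is given. Section 2.8.1.2 makes all three the outcome groups: "Outcome measures include vaccine coverage among the three target groups before / early in the intervention versus during its full implementation".

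Section 2.8.1.3 defines coverage as a share of a cohort. For the first two vaccines it counts those who "received the vaccine within the influenza season (influenza or pneumococci". For the remaining two, the dose must instead have been given in adulthood: "or as a single dose as an adult (meningococci and haemophilus influenzae type b". No separate paediatric definition appears.

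**The concern.** The term target population means adults at risk in Section 2.3 but takes in toddlers in Section 2.8.1, where it carries the primary hypothesis. Two things follow.

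First, for two of the four vaccines the stated measure cannot register any vaccination in the paediatric group, so those results would say nothing about the campaign.

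Second, for the vaccines that can be measured in children, the plan gives no reason to expect an effect, yet the result would stand as a primary result. The evaluation spans the pandemic, and the Discussion concedes that its effects could not be addressed in advance by the design. If infant vaccination moved differently in Berlin and Brandenburg than elsewhere for unrelated reasons, that movement could be reported as the campaign working or failing on its primary outcome.

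**Working it through.** The primary outcome has no stated sample size, power, effect size or significance level, so there is no figure to reproduce. The check compares the sections and then applies the coverage definition to each vaccine in the paediatric group.

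**Population**

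- Section 2.3: the campaign target is adults with risk factors, and no children are listed.
- Section 1 (Background): age under 1 is named as a sepsis risk factor, but Section 2.3 does not carry it into the target population.
- Section 2.8.2: the survey for the secondary outcomes recruits from age 18 upwards, consistent with Section 2.3.
- Sections 2.6.3 to 2.6.5: the campaign elements address the general public, health professionals, risk groups, and family members caring for a relative. None is described as aimed at parents of small children or at childhood vaccination.
- Section 2.8.1: children aged three and younger are nevertheless one of three primary-outcome groups.

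**Definition**

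Coverage = (cohort members meeting the vaccination definition) / (cohort members).

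- Meningococci and Hib: the definition needs a dose received as an adult. In a cohort of n children aged three or younger the numerator is 0, so coverage = 0/n = 0% for any n, in either region and in either period. The before-after difference between regions is (0 − 0) − (0 − 0) = 0, whatever vaccination took place.
- Influenza and pneumococci: the definition needs a dose within the influenza season and has no age limit, so it can be computed in children as worded. The document does not show whether a seasonal window suits this age group for pneumococci.

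The stated definition is therefore impossible to meet for two of the four vaccines in group (b).

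**Group (c)**

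This group has no age limit. If it includes minors, they too enter the denominator for meningococci and Hib without any chance of entering the numerator. Deleting group (b) alone would therefore not make the primary outcome adult-only.

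**The case against.** The best case for the plan has four parts.

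1. **Indirect exposure.** Addressing the general public is a named strategy in Section 2.4. The website, outdoor advertising and pharmacy material (Sections 2.6.2 and 2.6.3) were open to everyone, and clinicians were trained on recommended vaccines (Section 2.6.4). Parents and the clinicians who vaccinate children could have been reached. This stands. A reader might infer that the paediatric group cannot show a campaign effect. The documents do not support that; they support only that no targeting or mechanism is documented.

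2. **No defined family and no pooling.** A reader might multiply four vaccines by three groups and conclude that a fixed share of the primary results is void, or that a true adult effect is diluted. Neither is supported. Section 2.8.1.1 says only that coverage can be calculated in these groups, Section 2.3 ties meningococcal and Hib vaccination to asplenia, and no test family, weighting or pooling rule is given. Under pooling with no effect in children, the retained effect would be 1 − w, where w is the share of children: 97% at w = 3%, 90% at w = 10%, 67% at w = one third. These shares are assumptions, and the document gives neither w nor a pooling rule. If the groups are analysed separately, the adult results are untouched.

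3. **Condensed article.** Paediatric definitions may sit in a fuller plan that is not shown. That is possible, and the absence of such a definition would not by itself be a finding. What remains is that the definition the article does state conflicts with a population it also states.

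4. **Late change.** Removing a group from a registered primary outcome once some coverage data have been analysed (Section 2.9) could look data-driven. This is a fair caution. It bears on how the change is recorded and does not remove the conflict.

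**Conclusion.** The point holds in a limited form. One of the three primary-outcome groups is outside the population Section 2.3 says the campaign targeted. For meningococci and Hib, two of the four vaccines, the stated definition gives 0% in that group whatever happens. For influenza and pneumococci the result can be computed, but it has no documented link to the campaign, so a regional shift in infant vaccination could be misread as a primary success or failure.

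The conclusion rests on the wording of Sections 2.3, 2.8.1.1, 2.8.1.2 and 2.8.1.3 alone and assumes that the adult-dose definition is meant to apply to every outcome group, since no other is given. No loss of power or dilution can be put on it from the documents. It still deserves correction, because it concerns who is in the primary outcome and what is counted there.

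**What to change.** Reconcile Sections 2.3, 2.8.1.1, 2.8.1.2 and 2.8.1.3 as follows.

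- Test the primary hypothesis in adults only: group (a), and group (c) with an explicit restriction to adults.
- Move group (b) out of the primary outcome. Report it as a non-primary comparison group, with coverage definitions suited to the age group for each vaccine analysed.
- Present the same regional difference in change for group (b) beside the adult results. State that it is an imperfect comparison, because parents and clinicians may have been exposed to the campaign; it can flag a regional shift but cannot be used to correct the adult estimate.
- Record the change as a dated amendment, disclosed in the registry entry and in the results paper, before the final analysis. State which interim coverage data had been seen by then, since Section 2.9 describes intermittent coverage analyses and reports findings from 2021/2022. Section 3.1 describes primary data collection as unfinished; if the final analysis has since been run, label the change as made afterwards.

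The cost is wording, an age filter on group (c), and a small additional analysis for group (b) on claims data the analysing institute already receives routinely. No stated sample size or power figure changes, because none exists for the primary outcome. The main downside is the appearance of a late outcome change, which the dated disclosure is meant to address.

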#### 2.8.2 Assessment of the secondary outcome

Secondary outcome is assessed by the partners at the Jena University Hospital in a longitudinal survey of risk groups.

*2*.*8*.*2*.*1 Data source and sample*. The survey was conducted at three measurement points before, during, and after the implementation of the information campaign, in March—July 2021 (before), March—July 2022 (during) and March—July 2023 (after). All parts of the survey were conducted both in the intervention regions and the remaining German states as the control condition. The evaluation of secondary outcomes is based on the first and third time point, while the second time point served to inform the process evaluation of the campaign (see 2.9.).

A convenience sample of *n* = 740 persons with a minimum age of 18 years was recruited by the market research institute IPSOS. The recruitment was designed to achieve predefined numbers of cases within strata defined by age (<60 years, ≥60 years), education (low, middle, high), specific chronic diseases (e.g., diabetes, chronic diseases, cancer), and regions (intervention vs. control states). Sample recruitment for persons without chronic diseases was realized via an existing consumer survey panel. Sample recruitment for the group of persons with specific diseases, sample recruitment was carried out via self-help groups, general practitioners, social media and by contacting participants of previous studies by IPSOS. After they gave informed consent to participate in the survey study, participants were interviewed online, via telephone or face-to-face, using a standardized questionnaire in German language.

*2*.*8*.*2*.*2 Sample size considerations*. As the sample size required for the analysis depends on a number of factors (e.g. stability of the outcomes between the survey time points, variance of the outcomes at the survey dates, the intervention effect, which cannot be specified precisely in advance), several scenarios were considered as part of a simulation study. The power simulation was conducted in the statistical software R [26] version 4.0.2) with the R package lme4 [27]. As result a sample size of *N* = 244 for the third survey time point seems to be sufficient for detecting a moderate effect (*d* = 0.5) at a significance level of α = 0.05 with a power of 80%, even with low stability of the outcome variables (correlation of *r* = 0.3 between survey time points). However, the resulting sample size is only sufficient under the assumption that there are no missing values on relevant variables. To allow for a reduction in the effective sample size due to missing values, the sample size estimated from the simulation study was increased by 15%, resulting in a sample size of N = 280.

A necessary condition for the planned analyses and the power simulation carried out is the participation at both, first and third, survey time points. For this reason, the dropout rate must be taken into account for the sample size consideration. Based on the experience from the market research institute a drop-out of about 60% from the first to the third survey time point was used, resulting in a total sample size of *N* = 740 for the first time point.

*2*.*8*.*2*.*3 Outcomes*. We developed a questionnaire to assess sepsis knowledge, ability to detect sepsis as an emergency, and attitude towards vaccination (secondary outcomes). Sepsis knowledge was assessed in the following five domains using an adaption and extension of an existing instrument (8): definition and epidemiology (12 items), general prevention (3 items), symptoms (7 items), risk factors (7 items), and sepsis-specific vaccination knowledge (7 items). To measure the ability to detect sepsis as an emergency, five case vignettes were developed including typical sepsis-related medical emergencies (e.g., sepsis due to urinary tract infection or sepsis due to respiratory infection), for which participants had to rate how they would react in the described situation using an ordinal three-step-scale (0—“Wait one day and decide then”, 1—“Visit the general practitioner on the same day”, 2—“Call the emergency service or go to the emergency department”). Vaccination behavior and attitude towards vaccination was assessed based on the Theory of planned behavior [28] and the 5C-model [29]. For the above-mentioned outcomes, an item pool and first draft of the questionnaire was created. Content validity, relevance and comprehensibility of the questionnaire were evaluated by cognitive interviews with experts in the field of emergency medicine, infectious diseases, intensive care medicine and psychiatrics (n = 5), and one patient, and the questionnaire was revised based on the results. A pretest of the revised questionnaire was conducted in a pilot survey among members of patient support groups for chronic diseases (n = 71) and item characteristics as well as number of missing responses were investigated. Based on the results of the pre-test, we modified minor details of the questionnaire to receive the final draft. The questionnaire was administered in German language.

*2*.*8*.*2*.*4 Statistical analysis*. To assess the effect of the intervention in the controlled before-after design, a linear mixed model will be calculated with the variables survey time point (first and third time point) and region (intervention and control region). The hypothesis of campaign effectiveness is examined by testing the interaction effect between survey time and region against zero. Survey time point, region and the interaction effect are estimated as fixed effects. Systematic differences between persons are taken into account as random effect. Differences in confounders between the control and intervention regions are adjusted by including the following confounders as covariates in the model: presence of chronic disease, age, gender, education level, health information seeking behavior (frequency of health information seeking and variety of information sources). Since 15% of missing values were already taken into account in the sample size consideration, list wise deletion is used in the analysis to deal with missing values. The analyses will be conducted with statistic software R and the R package “lme4” with a significance level of α = 0.05.

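### The survey uses three interview modes but the secondary-outcome model has no mode term, so a mode shift that differs between regions would bias the time-by-region test

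*Protocol article*

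**What the plan says.** All of this comes from section 2.8.2 of the protocol article.

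- **Mode (2.8.2.1):** "participants were interviewed online, via telephone or face-to-face, using a standardized questionnaire in German language". The split by wave or region is not given, nor whether a person kept the same mode.
- **Regions (2.8.2.1):** "All parts of the survey were conducted both in the intervention regions and the remaining German states as the control condition".
- **Waves analysed (2.8.2.1, 2.8.2.2):** "The evaluation of secondary outcomes is based on the first and third time point", that is 2021 and 2023. The analysis and its power simulation require "participation at both, first and third, survey time points".
- **Test (2.8.2.4):** effectiveness is examined by "testing the interaction effect between survey time and region against zero". On the random part of the model: "Systematic differences between persons are taken into account as random effect".
- **Covariates (2.8.2.4):** the list is "presence of chronic disease, age, gender, education level, health information seeking behavior (frequency of health information seeking and variety of information sources". Interview mode does not appear.

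**The concern.** The outcomes in 2.8.2.3 could plausibly depend on how they are collected. Sepsis knowledge is a test of 12 + 3 + 7 + 7 + 7 = 36 items, and someone answering alone online can look answers up more easily than someone facing an interviewer. Attitude towards vaccination is open to social desirability when an interviewer is present. The argument is weaker for the five vignettes, which ask what the respondent would do. The article gives no size for any mode effect.

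Mode can change within a person between the two analysed waves. The person random effect absorbs only stable differences. With both waves complete, a covariate that is constant within a person and enters as a main effect adjusts levels but does not move the time-by-region estimate. If the mode mix changed differently in the two regions, the interaction would therefore contain a measurement artefact that the stated model does not remove. That interaction is the test of campaign effectiveness for knowledge, detection and attitude.

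**Working it through.** **The plan's own figures.** The point disputes none of them; N = 244 serves only to scale the results. 244 × 1.15 = 280.6, which matches the stated 280. 280 / 0.40 = 700 against the stated 740, an implied dropout of 1 − 280/740 = 62%, consistent with about 60%. The 244 itself comes from a simulation whose allocation and other settings are not given. A simple change-score formula with 1:1 allocation, two-sided, gives 176, so 244 could not be reproduced. Power at 244 by that formula is 91% (1:1), so the statement that it suffices is not contradicted.

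**Inputs from the article (2.8.2.2):** N = 244, d = 0.5, α = 0.05, r = 0.3 between waves.

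**Assumed inputs:** 1:1 allocation, a two-sided test, a mode effect m in SD units, and the change in mode share in each region. The article gives none of these.

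**Step 1: bias.** With two complete waves the interaction is a difference in mean change:

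bias = m × [(change in mode share, intervention region) − (change in mode share, control region)]

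- Mode constant within each person: both changes are 0, so the bias is 0, even if the regions use different modes.
- Same shift in both regions: the difference is 0, so the bias is 0.
- 10-point differential, m = 0.3: 0.10 × 0.3 = 0.03 SD, and 0.03/0.5 = 6% of the planned effect.
- 30-point differential, m = 0.6: 0.30 × 0.6 = 0.18 SD, and 0.18/0.5 = 36%.

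**Step 2: standard error.** SD of change = √(2 × (1 − 0.3)) = 1.183. SE = 1.183 × √(2/122) = 0.151.

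**Step 3: type I error.** Formula: 1 − Φ(1.96 − bias/SE) + Φ(−1.96 − bias/SE).

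| Differential shift | m (SD) | Bias (SD) | Type I error |
|---|---|---|---|
| 0 | any | 0 | 5.0% |
| 10 points | 0.3 | 0.03 | 5.5% |
| 30 points | 0.3 | 0.09 | 9.1% |
| 30 points | 0.5 | 0.15 | 16.8% |
| 30 points | 0.6 | 0.18 | 22.1% |

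**Step 4: simulation.** 2,000 replicates, N = 244, 1:1, r = 0.3, two mode categories, analysed as change scores without and with the change in mode as a covariate.

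| Scenario | m | Without mode: bias, type I | With mode: bias, type I |
|---|---|---|---|
| Constant per person, regions 20% vs 50% | 0.3 | 0.002, 5.3% | 0.003, 4.8% |
| Same, m larger | 0.5 | 0.004, 4.5% | −0.004, 5.4% |
| 10% to 40% in both regions | 0.3 | −0.003, 4.9% | −0.002, 3.7% |
| Same, m larger | 0.5 | 0.000, 3.9% | −0.005, 5.2% |
| 30-point differential | 0.3 | 0.086, 8.9% | 0.000, 4.2% |
| Same, m larger | 0.5 | 0.147, 15.2% | −0.004, 5.5% |

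The first two scenarios stay unbiased without any mode term. Only the differential shift biases the test, and adjusting for mode removes that bias. In these runs mode was unrelated to stable differences between persons.

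**Step 5: noise from an equal shift.** If 30% of persons switch mode and m = 0.5, the variance of change grows by 0.5² × 0.3 × 0.7 = 0.0525 on 1.4, or 3.75%. This is a small loss of precision.

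**The case against.** **The pandemic reading.** A reader might infer that the first survey fell under contact restrictions and the third did not, so that easing alone would look like a campaign effect. Section 2.7 does say that "in-person formats only became possible when contact restrictions due to the pandemic subsided", but it is describing campaign formats, not survey interviews. Nothing in the article says that face-to-face interviews were unavailable in 2021 or that the mode mix had changed by 2023. Even if it had, a shift shared by all states cancels in the interaction. This objection stands, and the stronger reading has no support.

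**Silence is not evidence.** The article gives one condensed sentence on mode, which is equally compatible with each person keeping one mode. Fieldwork rules may sit in a fuller document that is not shown. This also stands: the article cannot be faulted for failing to describe mode control. What remains is the covariate list, which the article does state and which leaves mode out.

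**No mechanism for a regional difference.** The article suggests none. Recruitment through several channels and about 60% planned dropout leave room for the mode mix of those analysed to move differently by region, but that is a possibility only.

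**Assumed magnitude.** Both inputs are assumed. The lower end of the range barely moves the type I error, and the upper end needs a large regional divergence and a large mode effect together.

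**Covariates that vary over time.** Age, chronic disease and information seeking can also change over two years, and the article does not say whether they are held at baseline. Mode is therefore not the only item that could vary within a person, but it is the one with no term in the model.

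**Conclusion.** The point holds in a conditional form. Three interview modes are in use, the stated model has no mode term, and a change in mode mix that differs between the regions would pass into the tested interaction. The bias is 0.03 to 0.18 SD under the assumed 10 to 30 point differential and 0.3 to 0.6 SD mode effect. With N = 244 at 1:1 allocation, that puts the type I error between about 5.5% and 22%. With no differential shift the bias is zero and the type I error is nominal.

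Whether such a shift occurred cannot be told from the article. The primary outcome rests on claims data and is untouched. This is a low-priority improvement to the secondary analysis and not a flaw that invalidates it.

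**What to change.** In section 2.8.2.4:

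1. Tabulate interview mode by region and wave for the persons analysed. If the mix is stable, or moves in parallel, the table largely settles the question.
2. Add interview mode at each wave as a three-level, wave-specific covariate in the mixed model.
3. Optionally, repeat the interaction test among persons interviewed in the same mode at both waves. Label this as supportive only, because it shrinks a sample already planned for about 60% dropout and conditions on something determined after baseline.

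The cost is 2 degrees of freedom and one table. No new data are needed if the survey institute recorded mode at each wave, which the article does not say and which should be confirmed first. If mode was in fact stable, the added term does no harm. Section 3.1 reports that the survey evaluation was not yet finished, so the change could still be made when the article was written.

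### Person-constant covariates entered without time interactions leave the time-by-region effect unchanged, so the stated adjustment does not guard the secondary outcomes against confounder-dependent change

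*Protocol article*

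**What the plan says.** Section 2.8.2.4 of the protocol article describes a linear mixed model for the secondary outcomes.

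- Test: "The hypothesis of campaign effectiveness is examined by testing the interaction effect between survey time and region against zero".
- Fixed part: "Survey time point, region and the interaction effect are estimated as fixed effects".
- Random part: "Systematic differences between persons are taken into account as random effect".
- Adjustment: "Differences in confounders between the control and intervention regions are adjusted by including the following confounders as covariates in the model". The list is "presence of chronic disease, age, gender, education level, health information seeking behavior (frequency of health information seeking and variety of information sources").

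Section 2.8.2.1 limits the evaluation to two waves: "The evaluation of secondary outcomes is based on the first and third time point". Section 2.8.2.2 makes taking part in both of these waves a condition of the analysis, and Section 2.8.2.4 handles missing values by list-wise deletion. The natural reading is two rows per analysed person.

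The article names no covariate-by-time term, weighting or matching. It does not say at which wave the covariates that can change are taken.

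**The concern.** The regions were not randomised and the survey uses a convenience sample, so the article rightly wants to deal with regional differences in confounders. The effect being tested, however, is a difference in change. It is biased when people with different characteristics change at different rates and the regions differ in those characteristics. A covariate main effect models a difference in level, which the before-after contrast has already removed.

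If the plan is followed on its natural reading, the published effects on sepsis knowledge, emergency recognition and vaccination attitude would be called confounder-adjusted. For the person-constant covariates they would be the same as the unadjusted difference-in-differences.

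**Working it through.** **Inputs from Section 2.8.2.** Two analysed waves, complete pairs, a person random intercept, and fixed effects for time, region and their interaction. The planning values are d = 0.5, a between-wave correlation of 0.3, and N = 244 raised by 15%: 244 × 1.15 = 280.6, which agrees with the stated 280. The plan gives no figure for regional imbalance or for confounder-dependent change, so there is no figure of its own to reproduce on this point.

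**Algebra.** For person i at time t (0 or 1), with region R and person-constant covariates x:

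y(i,t) = α + βt + γR(i) + δtR(i) + θ'x(i) + u(i) + e(i,t)

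The within-person change is

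D(i) = y(i,1) − y(i,0) = β + δR(i) + e(i,1) − e(i,0).

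Both θ'x(i) and u(i) drop out. The within-person sums carry no information on δ, because γ is free. The estimate of δ is therefore mean(D, intervention) − mean(D, control), with or without x.

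If change depends on the covariates through a term λ'x(i)t, then

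E(estimate) = δ + λ' × (mean x, intervention − mean x, control).

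The main effect θ does not enter this bias. Only terms in t × x can remove it.

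**Simulation 1 (assumed inputs).** One data set of 252 pairs with no campaign effect. High education was 60% versus 40% between regions, and the trend was 0.5 SD steeper in the better educated. Expected bias: (0.60 − 0.40) × 0.5 = 0.10 SD.

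- Without covariates: 0.077 (SE 0.150).
- With education and age as main effects: 0.077 (SE 0.150), identical to six decimals.
- With covariate-by-time terms: 0.017 (SE 0.157). SE ratio: 0.157/0.150 = 1.047.

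**Simulation 2 (assumed inputs).** REML random-intercept fits, 30 data sets per scenario, no direct campaign effect, person plus residual variance 0.3 + 0.7 = 1. Chronic disease was 70% versus 40% with a trend 0.4 steeper. Mean education differed by 0.4 of a step, with a trend 0.2 steeper per step. Expected bias: 0.30 × 0.4 + 0.4 × 0.2 = 0.20.

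| Scenario | No covariates | Main effects | Covariate-by-time | Largest shift from main effects |
|---|---|---|---|---|
| 280 pairs, covariates fixed | 0.190 | 0.190 | 0.011 | 2e-14 |
| Pairs, information seeking and age updated | 0.208 | 0.203 | −0.008 | 0.07 |
| As above, campaign raises information seeking by 0.5 | 0.360 | 0.212 | 0.005 | 0.24 |
| 740 persons, drop-outs kept with one row | 0.177 | 0.173 | −0.031 | 0.08 |

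In the first row the standard errors were 0.144, 0.144 and 0.164; main effects changed the SE by at most 2e-6, and 0.164/0.144 = 1.14.

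In the third row, 0.5 × 0.3 = 0.15 of the interaction is a campaign effect acting through information seeking (the outcome rises 0.3 per unit). Main effects at updated values lowered the estimate by 0.360 − 0.212 = 0.148, which is about that part. Adding time interactions at updated values also removed it. The first-wave value is therefore as important as the interaction terms.

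**Range of bias.** It is zero if either the imbalance or the trend difference is zero. It is 0.10 under the first set of assumptions and 0.20 under the second, that is 0%, 20% and 40% of the planned 0.5.

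**The case against.** **The wording does not say main effects only.** Listing variables as covariates neither states nor excludes time interactions, and a fuller analysis plan could contain them. This stands as a limit on certainty. But the article names its fixed effects, includes one interaction among them, and states what the covariates achieve, so main effects are the natural reading.

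**A reader might infer that none of the listed confounders can alter the tested effect.** The documents do not support that. Information seeking can differ between waves and then does move the interaction. Persons with a single wave would also break the exact identity. List-wise deletion could be applied to rows instead of persons, although the condition on taking part in both waves points to pairs.

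**A reader might also infer that the campaign effect will be adjusted away through information seeking.** That holds only if third-wave values are used, and the article does not say so.

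**The article claims to adjust for differences in confounders, not for differing trends.** Differences in level are indeed gone from the tested effect. They are removed by the before-after contrast, however, and the covariates add nothing to that. Parallel trends remain an unprotected assumption.

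**Recruitment had target numbers by age, education, disease and region (Section 2.8.2.1).** This may reduce imbalance. The article does not say that the targets were equal between regions. Gender and information seeking are not among the listed strata, and about 60% drop-out is expected before the third wave, so balance among analysed pairs is not assured.

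**The bias sizes are constructed.** This stands. The trend differences have no source in the documents, and in the first illustration the expected bias of 0.10 is below one standard error (0.150).

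**Conclusion.** The point holds in a limited form. With two waves, complete pairs, a person random intercept and no covariate-by-time terms, gender, education, first-wave age and, in practice, chronic disease leave the time-by-region interaction unchanged. The stated adjustment therefore gives the tested effect no protection against change that depends on them. This part is exact algebra, confirmed numerically to 2e-14.

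The conclusion rests on reading the covariates as main effects and the analysis set as pairs; both are natural readings, not explicit statements. The size of any bias is unknown. The values 0.10 and 0.20 only illustrate assumed imbalance and trends, and a reader should not take them as the bias of this study. Information seeking is a separate, conditional problem that depends on the wave at which it is measured.

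This should be fixed, but only secondary outcomes are concerned. The primary outcome, vaccination coverage, comes from claims data and does not use this model.

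**What to change.** In Section 2.8.2.4, or in the analysis plan behind it:

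1. State that every listed confounder, including information seeking and chronic disease, enters at its first-wave value.
2. Add the interaction of survey time with each of them. Equivalent routes are a regression of the within-person change on region and first-wave confounders, or weighting the regions to a common first-wave covariate distribution.
3. State that the analysis set is persons with both waves, so that list-wise deletion removes persons and not single rows.
4. Report the unadjusted interaction as a sensitivity analysis.

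The cost is a change to the model formula and a few degrees of freedom. With chronic disease, age and gender at one each, three-level education at two and the two information-seeking measures at one each, that is 1 + 1 + 1 + 2 + 2 = 7 interaction terms, against 280 planned pairs. The standard error widened by about 5% with two covariates in the first illustration and by about 14% with the full list and stronger imbalance in the second. The actual figure depends on the imbalance found. Section 3.1 reports data collection as unfinished and evaluation as continuing, so at the time of the article the model could still be specified this way before analysis.
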